## Introduction

Childhood uveitis is a rare but significant chronic eye condition [1]. Whist childhood onset disease accounts for approximately 1% of cases seen in adult uveitis clinics [2,3], it accounts for 10% of cases of uveitis related sight impairment amongst adults [4,5]. This over-representation is compounded by the frequent presence of multisystem disorders amongst those with childhood onset uveitis [6]. A key example is Juvenile Idiopathic Arthritis (JIA), the most common childhood inflammatory arthropathy [7]. Uveitis affecting the front section of the eye (anterior uveitis) the most common extra-articular manifestation of JIA [8]. Childhood anterior uveitis can be asymptomatic, or occur in children too young to report symptoms, so children with JIA undergo regular eye surveillance examinations every few months [9].

The strongest predictor of poor outcomes in childhood onset uveitis is the presence of established ocular structural complications at presentation, i.e., delayed diagnosis [10]. The worsening international workforce shortfall in paediatric ophthalmology is an obstacle to timely diagnosis for this population [11]. Imaging-based disease surveillance, which could be undertaken in settings across primary to tertiary care [12], would address this shortfall in capacity, providing specialist level care (potentially closer to the child’s home) to facilitate timely diagnosis and reduce the burden of uveitis related visual impairment amongst children and the adults they become.

Optical Coherence Tomography (OCT) machines have been widely adopted in secondary care and primary care settings (including high street opticians), providing high resolution images of eye structures [13]. OCT of the anterior segment (AS-OCT) to detect inflammatory cells in the eye, the hallmark of anterior uveitis, has been shown to be repeatable and highly sensitive for childhood disease [14]. Work has also been undertaken to understand the normative findings in healthy children [15]. The implementation of this potentially transformational innovation needs robust evidence on safety and effectiveness.

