### Participants

Eligibility criteria comprise:

New diagnosis (within preceding 12 months) of JIAEligible for uveitis surveillance in line with national guidance (Table 1) [9]Aged between 2 and 12 years

**Table 1 pone.0316410.t001:** Guidelines for screening for uveitis in JIA by the Royal College of Ophthalmologists and the British Society for Paediatric and Adolescent Rheumatology (BSPAR).

First eye examination within 6 weeks of referral Two monthly intervals from onset of arthritis for 6 months Then 3-4 monthly eye examinations for time outlined below:	
**Age at onset**	**Length of surveillance**
Less than 3 years^a^	8 years
3-4 years^a^	6 years
5-8 years^a^	3 years
9-10 years^a^	1 year
Less than 6 years^b^	5 years
6-9 years^b^	2 years
Any age^c^	5 years

^a^- For oligoarticular JIA, Psoriatic arthritis onset and Enthesitis related arthritis (ERA).

^b^- For polyarticular, ANA + JIA onset <  10 years.

^c^- For polyarticular, ANA- JIA, onset < 7 years

Exclusion criteria comprise:

• Visual impairment or any ocular co-morbidities that would negatively impact on best corrected acuity• Developmental/learning difficulties that preclude concordance with examination/informed assent

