**Fig 1 pone.0316410.g001:**
[figure not shown]
SPIRIT schedule of assessments. ^a^ Visits for those within 6 months of diagnosis: newly diagnosed: Day 1, Week 8, Week 16, Week 28, Week 40, last visit Week 52.Visits for those entering study outside the 6-month widow: Day 1, Week 13, Week 26, Week 39, Week 52.^b^ Concomitant use of a. immunosuppression or immunomodulation (and dose); any eye or visual symptoms since last visit; any other parental concerns.^c^ Measured with age-appropriate method: Cardiff cards, Thomson Kays or Thomson LogMAR in each eye separately.^d^ Heidelberg Spectralis OCT2 and Optovue RTVue anterior segment cube and single line scans.^e^ A diagnosis of new onset uveitis at any visit results in exit from the trial.

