**Fig 2 pone.0316410.g002:**
[figure not shown]
Details about the specific procedures during the intervention and control arm. * - See supplemental document 2 (S2) for specific visual acuity screening protocol.

Exit from the study will occur either at visit 7 (for participants with a new diagnosis of JIA within 6 months of entrance to study), at visit 6 (for participants whose JIA was diagnosed within 6 to 12 months of study entrance, Fig 1), or at any visit where uveitis has been diagnosed. A diagnosis of uveitis will be made clinically, using slit lamp examination. Any child within the intervention arm in whom a ‘disease positive’ AS-OCT is acquired (i.e., more than 1 hyper-reflective particle in any cross-sectional scan) will undergo a confirmatory slit lamp examination. Confirmation of uveitis will lead to a child exiting the study.

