### Study outcome measures

The main outcomes of interest are the study feasibility metrics, specifically

- The proportion of patients within the service who meet the eligibility criteria, and reasons for exclusion

- The proportion of eligible patients recruited

- The proportion of patients who withdraw due to loss of consent or are lost to follow-up

- Statistical parameters (point estimates and range/ variance) of the clinical and patient centred outcome measures

The primary clinical outcome measured (as a surrogate endpoint) will be:

- Agreement, for participants in the intervention arm, of AS-OCT findings with routine clinical examination, analysed at 6 months and 12 months milestones

Other clinical outcomes of interest will be:

- New diagnosis of uveitis

- New diagnosis of other visual/ocular problems

We shall be evaluating patient centred outcomes, specifically

- Health related quality of life (PedsQL child self-report, at 12 months and change from

baseline to 12 months)

We shall also be evaluating resource use across the feasibility study to support the design of cost-effectiveness analyses in the larger scale study.

Adverse and serious adverse events (AE/SAE) will be recorded for both the intervention and routine care arms. These events comprise (1) Development of anterior chamber inflammation; (2) development of non-sight threatening sequalae of ocular inflammation during the study period; (3) progression or disease flare of JIA; (4) development of treatment related adverse events. AE/SAE occurring in the intervention arms will be used as criteria to determine progression to a full RCT. Specifically. the progression criteria will be defined using a ‘traffic-light’ system (green – criteria met, amber – minor changes needed, red – significant changes needed).

Recruitment

-Green – > 4 recruits/month-Yellow – 2-4 recruits/month-Red – < 2 recruits/month

Adverse events (incidence of sight threatening complications in imaging-based surveillance group)

-Green/ Yellow – No cases-Red – > 1 case

Adherence to surveillance programme

-Green – > 75%-Yellow – 30-75%-Red – < 30%

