### Analysis

Proportions will be reported as point estimates with 95% confidence intervals. Levels of missing data will be explored with respect to certain baseline characteristics, e.g., age and measures of disease severity to assess biases. All harms or unintended effects in each group will be reported. Initial trial success will be defined as: recruitment rates of > 4 recruits/month, or generation of information on barriers to recruitment; adverse event (incidence of new sight threatening complications in imaging-based surveillance group) rate of 0; adherence to surveillance programme of > 75% or understanding of barriers to adherence. We will seek to identify potential cost drivers to inform the collection of the data for cost-effectiveness analyses within a future definitive study. Within this feasibility trial, effect sizes (of ‘discrimination’ of disease) and variability in outcomes will be estimated with 95% confidence intervals to inform the sample size calculations for a full-scale trial. Efficacy and safety will be analysed according to randomisation group set, which will include all patients who underwent randomisation and who had recorded outcomes (positive detection) during the first 12 months or who completed at least 12 months of surveillance examinations. Missing outcomes (due to attrition) will be considered as an adverse outcome. We will compare the two study arms groups using two-by-two chi-square tests for equality of proportions for disease detection/ adverse outcomes within the OCT arm as compared with the ‘gold standard’ slit lamp examination group.

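### Quality of life rests on child self-report at 12 months, which the youngest entrants cannot give and which is lost for children diagnosed with uveitis before Week 52

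*Protocol article*

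**What the plan says.** All references are to the protocol article.

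- **Outcome.** Study outcome measures gives a single patient-centred outcome: "Health related quality of life (PedsQL child self-report, at 12 months and change from" baseline to 12 months. The reporter is the child. No parent-proxy form, lower age limit or age-restricted subset is mentioned.
- **Age.** The Participants section admits children "Aged between 2 and 12 years".
- **Age adaptation elsewhere.** Visual acuity is "Measured with age-appropriate method: Cardiff cards, Thomson Kays or Thomson LogMAR in each eye separately" (Fig 1, note c). No matching provision is stated for the PedsQL.
- **Exit.** Fig 1, note e: "A diagnosis of new onset uveitis at any visit results in exit from the trial". The text under Fig 2 repeats it: "Confirmation of uveitis will lead to a child exiting the study". No follow-up after exit is described.
- **Last visit.** Week 52 in both schedules; for later entrants, "Visits for those entering study outside the 6-month widow: Day 1, Week 13, Week 26, Week 39, Week 52".
- **Analysis set.** It includes randomised children "who had recorded outcomes (positive detection) during the first 12 months or who completed at least 12 months of surveillance examinations".
- **Use of the data.** Point estimates and variances of the clinical and patient-centred outcomes are among the main feasibility outcomes. The Analysis section says variability estimates will inform the full trial's sample size and that potential cost drivers will be identified.

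**The concern.** Two separate rules remove PedsQL data, and neither loss is random.

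The first acts through age. The outcome names the child as reporter, yet entry is open to children who cannot fill in a questionnaire about themselves. The second acts through the disease. A child diagnosed part-way through the year leaves the study and, as written, contributes nothing more. That child has no 12-month score or change score, and resource use and complications arising after diagnosis are not captured. These are the children who have the event that surveillance exists to detect.

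What is at stake is the information this trial is run to supply. A PedsQL mean and variance drawn mainly from older children without a diagnosis before Week 52 may not describe the population of the full trial. Cost data that stop at diagnosis leave out what follows a positive detection. Scores not collected at the time cannot be recovered by later analysis.

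**Working it through.** The article states no figure for PedsQL completeness and bases its sample size on no formal power calculation, so there is no figure to reproduce. The check sets the outcome definition against the entry and exit rules, then illustrates the size.

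**Step 1: age.** A change score needs self-report at entry and at 12 months. A child of 2 cannot give the first. The Participants section does not screen such children out, because its assent-related exclusion is tied to developmental or learning difficulties, and the Recruitment section seeks assent only where appropriate.

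**Step 2: exit.** The 12-month score falls at Week 52. A child diagnosed at any earlier visit has left by then. A child first diagnosed at the Week 52 visit can still complete the questionnaire there, so the loss applies to diagnoses before Week 52.

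**Step 3: analysis rules.** The analysis set retains children with a positive detection in the first 12 months. The missing-outcome rule counts outcomes lost through attrition as adverse. That can be applied to a yes/no outcome but does not define a PedsQL score. Children diagnosed before Week 52 are therefore in the set with no PedsQL value and no rule for one.

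**Step 4: size (illustration).** Input from the document: N = 80 (Abstract). Assumptions: share too young to self-report at entry, y = 20-40%; share diagnosed before Week 52, u = 5-20%; y and u independent; no other loss.

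Children with a change score: n = 80 × (1 − y) × (1 − u). The 95% CI half-width for a difference between equal arms, in SD units, is 1.96 × √(4/n).

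| y | u | n | Loss | Half-width (SD) |
|---|---|---|---|---|
| 0 | 0 | 80 | 0% | 0.44 |
| 20% | 5% | 80 × 0.80 × 0.95 = 60.8 | 24% | 0.50 |
| 20% | 20% | 80 × 0.80 × 0.80 = 51.2 | 36% | 0.55 |
| 40% | 5% | 80 × 0.60 × 0.95 = 45.6 | 43% | 0.58 |
| 40% | 20% | 80 × 0.60 × 0.80 = 38.4 | 52% | 0.63 |

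**Step 5: 12-month score alone.** The loss is smaller than for the change score, because some children become able to self-report during the year. For example, take ages spread evenly over the 11 single years from 2 to 12, self-report not possible at ages 2-4, and 10-20% diagnosed before Week 52:

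- Change score: 3/11 too young at entry, loss 1 − (8/11 × 0.90) = 35% to 1 − (8/11 × 0.80) = 42%.
- 12-month score: 2/11 still too young at 12 months, loss 1 − (9/11 × 0.90) = 26% to 1 − (9/11 × 0.80) = 35%.

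**The case against.** **Low stakes in a feasibility trial.** Recruitment and attrition are the primary outcomes, PedsQL enters no progression criterion, and no power calculation depends on it. The Analysis section already plans to examine missing data by age and disease severity. This limits the consequence but does not remove it. The patient-centred estimates are themselves a listed main outcome, and exploring missingness would reveal the age gap without filling it or repairing the loss through diagnosis.

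**Article limits.** Figs 1 and 2 are not shown, and the full protocol may hold a proxy form or an exit questionnaire. That is possible. The outcome as published still names child self-report at 12 months and would need correcting to match.

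**Stronger readings that the document does not support.**

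- A reader might infer that every child who develops uveitis lacks the score. Those first diagnosed at Week 52 need not, and the intervention arm has a standard examination scheduled at 12 months.
- A reader might take the Introduction's remark that uveitis can "occur in children too young to report symptoms" as an admission that self-report will fail. It is background on eye symptoms, not on the PedsQL or this trial's participants.
- A reader might infer that the safety progression criterion misses all complications in diagnosed children. Those present at the diagnosing visit can be recorded before exit; only later ones are lost, and these may also reflect treatment after diagnosis.
- A reader might treat a percentage loss as established. The article gives no age mix, no uveitis incidence and no minimum age for self-report. The surveillance table mostly covers younger onset, which could raise the young share. The Abstract's exclusion of those unable to complete examinations or give assent could lower it.

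**Conclusion.** The point holds for the youngest entrants and for children diagnosed before Week 52. Followed as written, the plan cannot obtain a PedsQL change score from either group. It also stops recording resource use and new complications at diagnosis while keeping the diagnosed children in the analysis set. The loss through diagnosis is informative, because it depends on the event under study.

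The existence of the gap needs only one assumption beyond the text: that a 2-year-old cannot complete a self-report questionnaire. Its size cannot be derived from the article. The 24-52% range for the change score, with the half-width rising from 0.44 to between 0.50 and 0.63 SD, rests wholly on the assumed shares and their independence, and should be read as an illustration. This should be corrected, but it does not threaten the recruitment and attrition outcomes.

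**What to change.** 1. **Reporter.** Collect the parent-proxy PedsQL at baseline and 12 months, at least for children unable to self-report, and preferably for all so that one reporter spans the age range. Keep self-report in children able to give it, analysed separately, and state the age range to which it applies. Making proxy report the main outcome at every age is a preference and is not required; parents know the allocation too.
2. **Data after diagnosis.** State that a uveitis diagnosis ends randomised surveillance but not data collection. Obtain PedsQL, resource use and sight-threatening complications to Week 52 at routine visits, by post or from the hospital record. Report complications present at diagnosis separately from later ones.

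The cost is one short parent questionnaire at two time points, record abstraction for the diagnosed children (8-16 if 10-20% of 80 are diagnosed, an assumption), and a minor amendment to protocol and consent text. The clinical exit rule is untouched. The Dissemination section expects recruitment to run to April 2026; the change is worth most to children not yet enrolled, because a missed baseline score cannot be obtained later.

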## Abstract

Children with Juvenile Idiopathic Arthritis (JIA) are at a currently unpredictable risk of a blinding, often asymptomatic, co-existent eye disorder, anterior uveitis which requires prompt treatment. The unpredictability of this insidious disorder commits children with JIA to three-monthly expert clinical examinations in specialist eye centres often located far from their homes. Optical coherence tomography of the ocular anterior segment (AS-OCT) has been shown to be an acceptable, repeatable and sensitive modality for uveitis detection, but is not standard care. This feasibility randomised controlled trial (RCT) aims to inform a future full-scale RCT comparing current routine practice (expert slit lamp examination, SLE) to AS-OCT for the surveillance of uveitis in children at risk. Eighty children aged between 2 and 12 years old and diagnosed with JIA within the preceding year will be included. Participants with an existing diagnosis of uveitis, other ocular co-morbidities or those unable to complete examinations or provide informed assent will be excluded. Participants will be randomised to SLE (control) or AS-OCT (intervention) examination at a frequency consistent with the current national programme for childhood uveitis surveillance. Children in the intervention arm will also have standard examination at 6 and 12 months after study entrance. Outcomes of interest will be feasibility (recruitment and attrition rates), clinical metrics (proportion diagnosed with uveitis or other ocular disorders at 12 months after study entrance), quality of life outcomes (PedsQL), and resource use. Additionally, comparative analysis of AS-OCT versus SLE (‘gold standard’ reference testing) findings at 6 and 12 months for those in the intervention arm will provide the proof-of-concept data necessary to develop and undertake a larger scale trial. Trial registration: This trial has been registered with clinicaltrails.gov (NCT05984758).

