### Recruitment

Following identification through medical record review and confirmation of eligibility at routine clinical review, participants and their families will be approached postally, using posted participant information sheets, or by telephone, 1-2 weeks prior to the next planned outpatient attendance. Informed consent will be sought from parents of participants by a member of the research team within a week of being given the study documentation. Assent will also be sought from participating children where appropriate [18,19] (see supplemental material 3 (S3) for the consent and assent forms to be used in the study). To minimise participant attrition, after entering the trial families will receive telephone calls a few days ahead of each visit to support attendance, and financial support for travel costs.

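### The single recruits-per-month criterion mixes a one-off pool of already diagnosed children with continuing flow, so as an overall average it overstates the rate a site can sustain

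*Protocol article*

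**What the plan says.** All references are to the protocol article.

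- **Criterion.** Study design makes recruitment and attrition rates the primary outcomes. Study outcome measures sets the light at "Green – > 4 recruits/month" and "Yellow – 2-4 recruits/month", with red below 2. Analysis counts as initial success "recruitment rates of > 4 recruits/month, or generation of information on barriers to recruitment". Neither section states an averaging window or a starting point, or separates recruits by when they were diagnosed.
- **Who can enter.** Participants admits children whose JIA was diagnosed up to 12 months earlier. The Abstract gives the target: "Eighty children aged between 2 and 12 years old and diagnosed with JIA within the preceding year will be included".
- **Later entrants are planned for.** The Fig 1 legend has its own timetable: "Visits for those entering study outside the 6-month widow: Day 1, Week 13, Week 26, Week 39, Week 52". The text with Fig 2 has a separate exit visit for "participants whose JIA was diagnosed within 6 to 12 months of study entrance".
- **How they are found.** Recruitment begins "Following identification through medical record review and confirmation of eligibility at routine clinical review", with the family then approached shortly before the next outpatient attendance.
- **What thins the pool.** The Abstract's exclusions begin with "Participants with an existing diagnosis of uveitis, other ocular co-morbidities".
- **Timing.** Dissemination expects recruitment to finish by April 2026. No start date appears.

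**The concern.** When the site opens, children diagnosed during the previous year can already qualify, and record review will find them. That pool can be used once. Afterwards the site depends on new diagnoses and new referrals. One monthly figure adds the two sources together.

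The Introduction and Discussion say the study exists to supply recruitment information for a full-scale trial. The number of sites and the duration of that trial depend on the opening pool, which counts once per site, and on the flow, which accumulates with time. An average over a fairly short feasibility period gives neither, and it lies above the flow whenever any of the pool enrols.

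**Working it through.** **Inputs from the article:** target 80; green strictly above 4 per month; yellow 2 to 4; eligibility window 12 months. The article derives neither the threshold nor the target, so there is no stated calculation to reproduce.

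**Assumptions:** a steady flow of f recruits per month from new cases, and a share s of the 12-month pool enrolled. The article gives neither.

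**Step 1. Time limit for green.** 80/4 = 20 months, so green over the whole period needs all 80 in under 20 months.

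**Step 2. Overall rate.** The pool supplies 12sf children and T months of flow supply fT. Setting 12sf + fT = 80 gives T = 80/f − 12s, so

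overall rate = 80/(80/f − 12s).

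**Step 3. Flow above which the light reads green.** T < 20 requires f > 80/(20 + 12s).

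| Share of pool enrolled | Flow must exceed |
|---|---|
| 100% | 80/32 = 2.50 |
| 85% | 80/30.2 = 2.65 |
| 75% | 80/29 = 2.76 |
| 50% | 80/26 = 3.08 |
| 25% | 80/23 = 3.48 |
| none | 80/20 = 4.00 |

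**Step 4. Overall rate for flows that are yellow on their own.**

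| Flow | s = 100% | s = 75% | s = 50% |
|---|---|---|---|
| 2.50 | 80/20.0 = 4.00 (yellow) | 80/23.0 = 3.48 (yellow) | 80/26.0 = 3.08 (yellow) |
| 2.75 | 80/17.1 = 4.68 (green) | 80/20.1 = 3.98 (yellow) | 80/23.1 = 3.46 (yellow) |
| 3.00 | 80/14.7 = 5.45 (green) | 80/17.7 = 4.53 (green) | 80/20.7 = 3.87 (yellow) |

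**Step 5. Uptake needed for green,** s > (80/f − 20)/12: above 56% at f = 3, above 76% at 2.75, and above 100% at 2.5, which is impossible.

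**Step 6. Chance variation and slower entry.** Poisson simulation, 4,000 runs per setting, share of runs reading green:

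| Setting | f = 2.5 | f = 2.75 | f = 3 |
|---|---|---|---|
| Whole pool enters at once | 52% | 81% | 96% |
| Entry at a visit within 3 months | 20% | 52% | 78% |
| As above, with an assumed 20% lost to uveitis by month 12 | 9% | 31% | 61% |

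With no pool counted, a flow of 3 reads green in 0.8% of runs (20,000 draws).

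**Step 7. Effect on planning (illustration).** Assume 36 months at the same site with f = 3. With full uptake, the overall rate projects 5.45 × 36 = 196 children, while pool plus flow gives 36 + 108 = 144, an overstatement of 36%. At 75% uptake the figures are 4.53 × 36 = 163 against 27 + 108 = 135, or 21%.

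**Step 8. Calendar.** Twenty months back from the end of April 2026 is about the start of September 2024. The only earlier date in the article is the protocol version date of 18 October 2023, which is not a recruitment start. Counted from that date, about 30.4 months would give 80/30.4 = 2.6 per month, which is yellow.

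**The case against.** Several counter-arguments have force.

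- **The averaging rule is not stated.** An overall average is the natural reading of a recruits-per-month threshold, but it remains a reading, and the full protocol or analysis plan may define the rate. This stands, and the point is worded accordingly.
- **The pool is smaller and slower than 12 full months.** A reader might infer that every child diagnosed in the past year is eligible on opening day. The article does not support that. Age, surveillance eligibility and absence of uveitis are also required, and families are approached around their next attendance, so the pool enters over months and some children pass the 12-month limit first. The simulation shows how much this lowers the chance of a false green, though at a flow of 3 that chance stays well above the no-pool figure.
- **The opening period may be too long for green.** If recruitment began before about September 2024, 80 children by April 2026 average 4 or fewer per month whatever the pool. This stands. The average would still lie above the flow.
- **Green against yellow decides little.** Yellow calls only for small changes, Analysis also accepts information on barriers, the steering committee sees recruitment figures two or three times a year, and the share of eligible children recruited is reported. This limits the consequence, but none of these outputs is stated to separate pool from flow.
- **A full trial's sites would also open with a pool.** This is correct if the same window is kept, so the surge is partly transferable. It is still a one-off per site and does not grow with duration.

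**Conclusion.** The point holds as a modest one about how the criterion is fixed. It is not a contradiction or a calculation error. The documents support the mechanism: a 12-month window, identification by record review, a schedule for later entrants, and one undivided monthly figure. Read as an overall average, that figure is biased upwards as an estimate of the sustainable rate.

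The size depends on assumed steady flow and pool uptake. A fair statement is that a flow of about 2.65 to 3 per month can read green, given uptake above roughly 85% at the lower end and 56% at the upper, and completion in under 20 months.

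Two stronger readings are not supported. One is that a flow of 2.5 reads green: with the whole pool it averages exactly 4.0, which is yellow, and it crosses only by chance. The other is that the light will mislead at this site: without a start date or an expected flow, that cannot be shown.

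**What to change.** Keep the overall rate and its thresholds, since nothing shows that 2 and 4 were meant for newly diagnosed children only; applying them to flow alone could produce an undeserved yellow. In addition:

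1. State the period over which the rate is averaged.
2. Report recruits per month separately for children diagnosed before and after the site opened, or report the rate once the opening pool has been approached. The second form is useful at a referral centre, where a child diagnosed elsewhere before opening may arrive later and really belong to the flow.
3. Read the light alongside the post-opening rate.
4. Carry both the pool and the flow figure into the full-trial design.

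The cost is one extra tabulation. The diagnosis date is already needed to establish eligibility and the entry date to compute the rate, so no new data or visits are required. The downside is that the sustainable rate may look less favourable than the headline.

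### The safety progression rule gives no colour to exactly one sight-threatening complication in the imaging arm, and does not line up with the success definition or the adverse event list

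*Protocol article*

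**What the plan says.** All of this is in the protocol article.

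- **Colours (Study outcome measures).** The traffic-light system has three separate verdicts: "green – criteria met, amber – minor changes needed, red – significant changes needed".
- **Safety criterion (same section).** The counted event is given as "Adverse events (incidence of sight threatening complications in imaging-based surveillance group"; the bands are "Green/ Yellow – No cases-Red – > 1 case".
- **Adverse event list (same section).** The recorded adverse and serious adverse events are said to comprise four items. The first is anterior chamber inflammation. The second is "development of non-sight threatening sequalae of ocular inflammation during the study period". The last two are "3) progression or disease flare of JIA; (4) development of treatment related adverse events".
- **Link between list and rule (same section).** "AE/SAE occurring in the intervention arms will be used as criteria to determine progression to a full RCT".
- **Success definition (Analysis).** One component of initial trial success is an "adverse event (incidence of new sight threatening complications in imaging-based surveillance group) rate of 0".

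**The concern.** A progression rule is fixed in advance so that every possible result already has its verdict when the data arrive. This one leaves out a result: one case is above the green/yellow condition and below the red one. Because green and yellow share the same condition, there is also no separate middle band into which a single case could fall. The Analysis section excludes one case from success but assigns no colour.

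This is the only safety criterion for progression, and it concerns the harm that matters most when imaging replaces slit lamp visits. The Introduction names structural complications already present at diagnosis as the strongest predictor of poor outcome. If one case occurred, the study team would have to settle the meaning of the rule after seeing the result.

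The adverse event list adds a smaller difficulty. It is said to feed the progression decision, but its only item on sequelae of inflammation is limited to those that do not threaten sight, while the criterion counts those that do.

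**Working it through.** **Step 1. Read the bands literally.** The article states no error rate or operating characteristic for this rule, so there is no figure to reproduce. The three progression rules can be set side by side.

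| Criterion | Red | Yellow | Green | Values without a colour |
|---|---|---|---|---|
| Recruitment per month | < 2 | 2 to 4 | > 4 | none |
| Adherence | < 30% | 30 to 75% | > 75% | none |
| Sight-threatening complications, imaging arm | > 1 | 0 | 0 | exactly 1 |

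The first two rules cover every value, including their boundaries. Only the safety rule has a hole, and only there do two colours share a condition.

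**Step 2. Compare with the Analysis section.** Success there needs a rate of 0.

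| Cases | Colour under Study outcome measures | Success component under Analysis |
|---|---|---|
| 0 | green/yellow | met |
| 1 | none printed | not met |
| 2 or more | red | not met |

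**Step 3. How often would the gap be reached?**

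Inputs:
- 80 children (Abstract), allocated 1:1 (Randomisation and allocation), so n = 80 / 2 = 40 in the imaging arm.
- True risk p per child: not given in the article. Assumed range 0.5% to 5%, with 10% as an outer value.

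Formulas, for independent children:
- P(0) = (1 − p)^40
- P(1) = 40 · p · (1 − p)^39
- P(2 or more) = 1 − P(0) − P(1)

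Example at p = 1%: P(1) = 40 × 0.01 × 0.99^39 = 0.270.

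| Assumed p | P(0): green/yellow | P(1): no colour | P(2 or more): red as printed | P(1 or more): red if one case counts |
|---|---|---|---|---|
| 0.5% | 81.8% | 16.4% | 1.7% | 18.2% |
| 1% | 66.9% | 27.0% | 6.1% | 33.1% |
| 2% | 44.6% | 36.4% | 19.0% | 55.4% |
| 2.5% | 36.3% | 37.3% | 26.4% | 63.7% |
| 5% | 12.9% | 27.1% | 60.1% | 87.1% |
| 10% | 1.5% | 6.6% | 92.0% | 98.5% |

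P(1) is largest at p = 1/40 = 2.5%, where it is 0.975^39 = 37.3%. It therefore stays below one half whatever the true rate. If only 30 children contributed, P(1) would be 13.0%, 22.4%, 36.0% and 33.9% at 0.5%, 1%, 2.5% and 5%, which is much the same picture.

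The last two columns show what depends on the missing colour. At an assumed 1%, the chance of red is 6.1% if one case is not red and 33.1% if it is.

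**Step 4. Compare the list with the rule.** None of the four listed items names a sight-threatening complication. The criterion nevertheless appears under an adverse events label, and the listed events are said to supply the progression criteria. The list and the rule do not match as printed.

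**The case against.** The strongest reply is that the text can be completed by elimination. No cases is the condition for both green and yellow, so one case meets neither and only red is left. The success definition points the same way. On this view the printed boundary is a slip for 1 or more. That stands as the most natural reading, and it is why a reader who infers that the committee would have no guidance at all goes too far. It does not remove the defect: the printed red band starts above 1, and the decision should not rest on inference once a case has occurred.

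It is also fair that success and traffic-light colour are different constructs. The Analysis section calls nothing a failure, and for recruitment and adherence it accepts information on barriers as an alternative route to success. The two sections are therefore misaligned at one case; they do not directly contradict each other.

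A reader might infer from the adverse event list that a sight-threatening complication would go unrecorded. The article does not support that. The criterion itself classes the event as an adverse event, the Analysis section counts it and promises to report all harms in each group, and new visual or ocular problems are a listed outcome. The imaging arm also has standard examinations at 6 and 12 months. What remains is a conflict of wording.

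A reader might also infer that an uncoloured result is the likely one, or that the gap puts participants at risk. Step 3 rules out the first. As to the second, these are criteria for a later trial, and a child with confirmed uveitis leaves the study whatever the colour.

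**Conclusion.** The safety criterion is wrong as written. It leaves exactly one case without a colour, gives green and yellow the same condition, and does not line up with the rate of 0 in the Analysis section. This follows from the wording alone and needs no assumption.

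The size does rest on assumptions: 40 children in the imaging arm, independent events, and a true rate that the article does not give. For 0.5% to 5%, the chance of landing in the gap is about 16% to 37%. That is plausible enough to settle beforehand, and never more likely than not.

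The mismatch with the adverse event list is real but secondary. The list conflicts with the rule it feeds; failure to capture the event is not shown.

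**What to change.** 1. In Study outcome measures, restate the safety criterion as: **Green – no cases; Red – 1 or more cases**, and state that this criterion has no yellow band. This gives every count one verdict and agrees with the rate of 0 in the Analysis section.
2. In the adverse event list in the same section, name sight-threatening complications of ocular inflammation as a recorded event, so that the list contains what the criterion counts.

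The cost is two lines of protocol text. Visits, data collection and sample size are unchanged. The first change should be made before any imaging-arm outcome is reviewed, so that the verdict for a single case is fixed independently of the data.
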